### Covariates

Several other variables are measured, such as the age of the caregiver, their sex, their relationship to the person with dementia (spouse, adult child, or other family member), level of education of the caregiver, living arrangement (living together or apart from the person with dementia).

All study data will be collected within the iSupport online tool using encryption for participant protection. Data are securely stored using a cloud-based encrypted platform. Data will only be accessed by project team members involved in data analyses. Confidentiality will be maintained before, during and after the trial. Study participants who discontinue use of the tool will be sent automatic weekly reminders to promote adherence. There is no external data monitoring board. The study team will take appropriate action in case any adverse effects are reported.

### Statistical analyses

Analyses will be conducted according to the intention-to-treat principle. Randomization efficacy will be assessed by examining characteristics in the iSupport condition compared to EOC and missing data and unbalance will be evaluated. Missing data on follow-up measurements will be imputed using multiple imputations. To examine the association between the experimental and comparison group on the primary and secondary outcomes, we will first calculate paired *t* tests and estimates of effect sizes will be calculated. By using multiple regression analyses, we can correct for possible confounders. With a “generalized estimating equations” (GEE) analysis the research question regarding the maintenance of the effectiveness of the intervention will be answered for primary and secondary outcomes in separate models [41]. Thus, all primary and secondary outcome measures will be analyzed using separate GEE models using each separate outcome measure as the dependent variable and an indicator for the intervention (the iSupport intervention compared to the education-only control) as the primary independent variable. Potential confounders will be added to these models. All analyses will be conducted using SPSS for Windows.

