## Methods and analyses

The trial design is a two-group RCT to establish the effectiveness of an online self-help training and support program (iSupport) compared to an education-only comparison condition (EOC) which provides education about dementia and caregiving through an on-line e-book (Fig. 1). The objective is to examine the effect of this online self-help training and support program on depression and anxiety outcomes. The RCT will last 6 months in total, including pre measurement (T0), first follow up (T1, 3 months after T0) and second follow-up (T2, 3 months after T1). The timeline of assessments and measures are described in Fig. 2.

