### Inclusion criteria

Participants are screened online to assess whether they are (1) aged 18 years and older, (2) are a self-reported caregiver of a person with dementia, (3) self-report that their family member has a diagnosis of Alzheimer’s disease or dementia (score ≥ 2 on the AD8) [28]. In addition, the caregiver should reside in India and have access to the Internet. For inclusion, the caregiver should experience some psychological distress, as indicated by some subjective burden (defined by a score of ≥ 4 on a 1-item burden scale ranging from 1 to 10) [29] or some symptoms of depression or anxiety (score ≥ 4 and < 15 on the Generalized Anxiety Disorder (GAD) Scale (7 items) [30] or ≥ 4 and < 20 on the Center for Epidemiologic Study-Depression (CES-D) scale (10 item) [31, 32]. If potential participants have a score of 20 or higher on the 10-item CES-D, and ≥ 15 on the GAD, caregivers are referred to the mental health services at NIMHANS or providers in their region. As this is an online intervention, and participants may be from all over India, no further referral or follow-up are given.

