### Randomization

After screening, participants who fulfil the inclusion criteria are requested to provide informed consent to enrol in the study. Next, they are asked to fill out the questionnaires at baseline, after which randomization is carried out using an automated computer-generated random number allocation, stratified by sex and relationship to the care recipient (spouse/other) with a block size of 2. Participants are masked to their intervention status.

To randomize the participants, a table is filled with “real random” 0 or 1 codes preceding the start of the project, drawn with equal probability (50%) from the Random.org site [33]. This table is subsequently linked to the table with the accumulation of participant data. Immediately before randomization, the questionnaire script determines what block-condition (male/female; spouse/no spouse) applies to the participant. Next, with a block size of 2, there are two options:If a new block must be opened for the new participant: the participant’s condition will be determined by the “real random” value in the linked table. Thus, if the random value is 0, the participant’s condition will be 0 and if the random value is 1, the condition will be 1If a block is already open and partially filled (thus, with a block size of 2, with one other respondent), the new participant’s condition will be the other condition of the first participant. So, if the first participant has condition 0, the new participant’s condition will be 1, etc.

Baseline characteristics of individuals randomized to either of the two conditions will be compared to ensure that randomization was successful. If an individual that is enrolled in the trial drops out after enrollment, is lost to follow-up or discontinued from the study, their data will be analyzed using the intention-to-treat principle.

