### Sample size calculation

Sample size calculation is guided by the primary outcome change in burden (ZBS) at 6 months after baseline. Alpha (two-tailed) was set at 0.05 power at 80%. A standardized effect size of .33 – a relevant effect for the Zarit Burden Scale (ZBS) [35] – was calculated using earlier findings from a recent trial which evaluates power/sample size for these studies [36]. Using Stata 12, minimum sample size for each group was identified as 80. To take account of study dropout we increase this number by 30% (*N* = 208; 104 per group).

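### The paired t tests named as the first between-group analysis measure only change within each arm, and the article does not say which later analysis decides

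*Protocol article*

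**What the plan says.** The Methods and analyses section sets the comparison: "The trial design is a two-group RCT to establish the effectiveness of an online self-help training and support program (iSupport"), against an education-only e-book. The Randomization section allocates individuals singly, with codes "drawn with equal probability (50%) from the Random.org site" and "stratified by sex and relationship to the care recipient (spouse/other) with a block size of 2". It describes no matching of participants for analysis.

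The Statistical analyses section then sets out three steps:

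1. "To examine the association between the experimental and comparison group on the primary and secondary outcomes, we will first calculate paired" t tests, with effect sizes estimated in the same sentence.
2. Multiple regression, described as a way to correct for possible confounders.
3. GEE models, one per outcome, introduced to answer whether effectiveness is maintained. The arm indicator is the main independent variable and potential confounders are added.

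The section does not say which of the three provides the primary result.

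**The concern.** The first step asks a between-group question and answers it with a within-person test. A paired t test of T0 against follow-up has no arm term, so it cannot estimate the effect that the trial was randomized to estimate.

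The setting makes this matter. Eligibility depends on symptoms: "For inclusion, the caregiver should experience some psychological distress", and the CES-D10 and GAD-7 serve both as entry routes and as primary outcomes. Some improvement through regression to the mean is therefore plausible in both arms, and the control arm also receives education. If both arms improve, separate paired tests can be significant in one and not in the other by chance alone. They can also be significant in both when iSupport truly adds something. Neither pattern measures the difference between arms.

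Effect sizes are also at stake. Sizing used "A standardized effect size of .33" for "Sample size calculation is guided by the primary outcome change in burden (ZBS) at 6 months after baseline". A pre-post effect size from one arm is not comparable with a between-arm effect.

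**Working it through.** **What each planned step can estimate**

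| Step | Stated purpose | Arm term stated? | Gives iSupport minus control? |
|---|---|---|---|
| Paired t test | association between the groups | no | no |
| Multiple regression | correction for confounders | not stated | only if arm is included |
| GEE | maintenance of effectiveness | yes | yes, in some form |

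The step assigned to the group comparison is the one that cannot make it. The step that can is introduced for a different question.

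**How far separate paired tests could mislead**

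The article gives no error rate for this approach, so there is no stated figure to reproduce.

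Inputs from the article:
- n = 80 analysed per arm and two-sided alpha 0.05 (Sample size calculation: "Alpha (two-tailed) was set at 0.05 power at 80"%). The 80 is taken as stated; whether it follows from the effect size is a separate question.

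Assumed inputs (the article gives none):
- correlation between T0 and T2 scores r = 0.6;
- the same true improvement s in both arms, in SD units of the score, so the true between-arm effect is zero.

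Formulas:
- SD of change = sqrt(2(1 − r)) = sqrt(0.8) = 0.894.
- Noncentrality of the paired t = s × sqrt(n) / 0.894.
- P = probability that the paired test is significant in one arm (noncentral t, 79 df).
- The arms are independent, so the probability that iSupport is significant and control is not is P(1 − P).

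| s | Noncentrality | P | P(1 − P) | Simulation (4,000 runs) |
|---|---|---|---|---|
| 0.1 | 0.1 × 8.944 / 0.894 = 1.0 | 0.17 | 0.14 | 0.149 |
| 0.2 | 2.0 | 0.51 | 0.25 | 0.247 |
| 0.3 | 3.0 | 0.84 | 0.13 | 0.136 |

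P(1 − P) cannot exceed 0.25, so the 0.2 SD case lies at the ceiling. The rate falls on either side of it.

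A second simulation (20,000 runs, 80 per arm) expressed the common change in SDs of the change score:

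| Common change | iSupport significant, control not | Exactly one arm significant | Two-sample t test on change significant |
|---|---|---|---|
| 0.2 | 24% | 48% | 5.1% |
| 0.33 | 14% | 28% | 5.0% |
| 0.5 | 0.7% | 1.4% | 4.7% |

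The between-arm test stays at about 5% throughout. The contrast between the two paired tests does not, and its rate depends on how much both arms happen to improve.

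**The case against.** The strongest answer is that the paired tests are only the first of three steps. The same section commits every primary and secondary outcome to a GEE model with arm as the main independent variable. This stands. A reader might infer that the plan has no between-group analysis, or that it discards the randomization. The text does not support that: the statement is true of the paired step alone.

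It is also fair that the article never states a rule of concluding benefit when iSupport is significant and control is not. The 25% and 14% apply only if someone reads the results that way. Nor are the 51% and 84% in the P column false-positive rates to set against 5%: they are the power to detect a within-arm change that the calculation makes real. The article does not state that both arms are expected to improve. Entry thresholds are low (4 or more on each scale), and burden eligibility uses a single item, not the Zarit scale. The size of any regression to the mean is therefore unknown.

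Two innocent readings were considered. With blocks of 2, a paired test across the two members of a block would compare arms, but the article uses blocks only for allocation and proposes no such analysis. The word paired may also be a slip for an unpaired test; if so, the sentence still needs correcting.

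What the later steps do not do is repair the first. The group comparison is given to the paired tests, the GEE is tied to maintenance, and nothing says which result decides.

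**Conclusion.** The concern holds for the first analysis step. For all primary and secondary outcomes, the article assigns the between-group question to a test that gives only within-arm change. This is a wrong method as stated, not a detail left to an analysis plan. It does not extend to the whole plan, because the GEE models carry an arm indicator.

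If the paired results were taken as the group comparison, an ineffective programme would show significance in iSupport alone in about 25% of trials at a common 0.2 SD improvement and about 14% at 0.3 SD. These figures assume 80 per arm, r = 0.6, and a way of reading the results that the article does not prescribe. They show what could go wrong and do not predict this trial's error rate. That a paired test gives no between-arm difference needs none of these assumptions.

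**What to change.** Replace the paired t tests with a between-arm comparison and name it as the one that decides.

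- **Primary outcomes:** regress the T2 score on arm, T0 score, sex and spouse/other (ANCOVA). The equivalent arm contrast at T2 from the planned GEE would serve as well. Report the adjusted mean difference, its 95% CI, and a standardized effect size computed from that difference.
- **Secondary outcomes:** make the same comparison, adjusting for T0 where a T0 value is collected. Table 1 as extracted shows no T0 mark for EQ-5D, mastery or self-efficacy. The extraction may have lost these marks, so the sponsor should check.
- **Within-arm changes:** descriptive only, without p values.

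The cost is a sentence or two in the analysis section. No new data are needed for the primary outcomes, which Table 1 lists at both T0 and T2. The Trial status section says enrolment was under way, so at that stage the change could still be made before analysis.

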### Outcomes

The primary outcomes are burden and symptoms of depression and anxiety (Table 1). Burden is measured by the 22-item Zarit Burden Scale [35]. Responses range from 0 (never) to 4 (nearly always). Depressive symptoms are measured using the modified version of the Center for Epidemiological Studies Depression scale (CES-D10): ten items measuring frequency of common depressive symptoms (e.g., sadness, hopelessness, sleep and appetite disturbances) in the past week. Response categories are: 0 (rarely or none of the time present) to 3 (most or all of the time present) [32]. Anxiety symptoms are measured using the General Anxiety Disorders scale (GAD-7), a 7-item measure rating the frequency of common anxiety symptoms (nervousness, worry, not being able to relax, being restless, annoyed or irritable, and feeling afraid that something awful will happen) in the past 2 weeks. Response categories are: 0 (not at all), 1 (several days), 2 (more than half the days) and 3 (nearly every day) [30].

**Table 1 Tab1:** Primary and secondary outcome measures and study variables in the iSupport online support trial

Outcome measures in the randomized controlled trial (RCT) (number of items, response scale, total scale score range)						
Primary	Target of scale	Reliability and validity of scales	Cronbach’s alpha	Pre measurement (T0)	First Follow up (T1)	Second Follow-up (T2)
Zarit Burden Scale (22, 0–4, 0–88)^a^	Perceived stress of caregiving	Intra-class correlation coefficient (ICC): 0.88 to 0.89	Cronbach’s α = 0.82 to 0.93	X		X
CES-D10 Center for Epidemiological Studies Depression Scale (10 items, 0–3, 0–30)^b^	Depression	Test-retest reliability (r values = 0.41 to 0.70)	Cronbach’s α = 0.80 to 0.85	X	X	X
GAD Generalized Anxiety Disorder 7-item scale (7 items,0–3, 0–21)^c^	Anxiety	ICC = 0.83	Cronbach’s α = 0.92	X		X
Secondary						
EuroQoL-5D Descriptive system of health-related quality of life states consisting of 5 dimensions (mobility, self-care, usual activities, pain/discomfort, anxiety/depression).^d^	Quality of Life	ICC = 0.70	No overall Cronbach's α reported		X	X
Mastery (7 items, 1–4, 7–28)^e^	Perlin 7-item Mastery Scale	Principal component factor loadings ranging from − 0.47 to 0.76			X	X
Self-efficacy (1, 0–5, 0–40)^f^	RIS Self-efficacy Scale	*r* = 0.48 to 0.69	Cronbach’s α = 0.72 to 0.79			X
Confounders/modifying Variables						

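### Each primary outcome is put through t tests, adjusted regression and a GEE with none named as deciding; for depression the deciding visit is open as well

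*Protocol article*

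**What the plan says.** The Statistical analyses section sets out three procedures for the comparison of iSupport with the education-only control.

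- First: "we will first calculate paired *t* tests and estimates of effect sizes will be calculated. By using multiple regression analyses, we can correct for possible" (that is, for confounding variables). That sentence pair covers both the t tests and the regression.
- Then a GEE. It is introduced to answer whether the effect lasts, but the section goes on: "all primary and secondary outcome measures will be analyzed using separate GEE models using each separate outcome measure as the dependent variable". The arm indicator is the main independent variable, and potential confounders are to be added.

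The section does not rank these procedures or say which prevails if they disagree.

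On timing, the Sample size calculation section states: "Sample size calculation is guided by the primary outcome change in burden (ZBS) at 6 months after baseline". That fixes a visit for burden only. In Table 1 (Outcomes), the row "CES-D10 Center for Epidemiological Studies Depression Scale (10 items, 0–3, 0–30)" is marked at T0, T1 and T2. The Zarit Burden Scale and the GAD-7 are marked at T0 and T2. No section names a deciding visit for depression.

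The error rate is given once: "Alpha (two-tailed) was set at 0.05 power at 80"%.

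**The concern.** This point is about the number of tests within one outcome. A raw change comparison, a confounder-adjusted difference and a GEE arm effect are different contrasts and can disagree. If none is designated, the analysts will hold several p-values for a single outcome, and the plan does not stop any of them from being reported as the trial's result. The type I error for that outcome is then above the stated 0.05. For depression, a reader could not tell what a positive result means if T1 and T2 disagree. Reducing the trial to one primary outcome would not close the gap, because that outcome would still have several candidate tests.

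**Working it through.** **Inputs.** From the document: two-sided alpha 0.05; three analyses per outcome; follow-up at T2 only for burden and anxiety, and at T1 and T2 for depression; 80 per group as the stated minimum. Assumed, because the document gives no value: between-visit correlation r = 0.3, 0.5 or 0.7, equal at all pairs of visits, with equal variances. Success is assumed to mean any p<0.05.

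**The plan's own figures.** The figure at issue is the 0.05. One named between-arm test at one visit, simulated under no effect with 80 per arm, gives 0.050 to 0.057 (4,000 runs per setting; simulation error about 0.004), so a single test holds its level. The 80 per group does not follow from effect size 0.33 by the usual two-group formula: 2 × ((1.96 + 0.842)/0.33)² = 2 × 72.07, which rounds up to 145. That is a separate matter. The large-sample false-positive rates below do not depend on n.

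**Step 1: the paired t test as written.** It compares visits within a group, so it says nothing about iSupport against the e-book. Suppose both arms improve by 0.3 SD (assumed) and r = 0.5. The SD of change is √(2 × (1 − 0.5)) = 1, the expected z is 0.3 × √80 = 2.68, and each arm is significant with probability about 0.76. One arm is then significant and the other not in about 2 × 0.76 × 0.24 = 0.36 of trials with no true difference (simulated 0.37). For the steps below, a between-arm t test on change replaces it.

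**Step 2: contrasts.** Write the arm differences at the visits as (T0, T1, T2).

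- Change at T2: weights (−1, 0, 1).
- Baseline-adjusted at T2: weights (−r, 0, 1).
- Correlation of these two: √((1 + r)/2) = 0.81, 0.87, 0.92 for r = 0.3, 0.5, 0.7.
- Correlation of the adjusted T1 and T2 tests: r/(1 + r) = 0.23, 0.33, 0.41.

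The quantity wanted is P(max |z| > 1.96) under no effect.

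**Step 3: burden (one follow-up).** If the GEE tests arm-by-time, with two visits it coincides with the change test, so two distinct tests remain. If the GEE tests an arm effect averaged over T0 and T2, it is uncorrelated with the change score and adds a nearly separate chance.

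| Tests that count | r = 0.3 | r = 0.5 | r = 0.7 |
|---|---|---|---|
| Change, adjusted | 0.078 | 0.073 | 0.068 |
| Same, plus GEE averaging in baseline | 0.114 | 0.113 | 0.110 |

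A full-data simulation with 80 per arm, covariates and a robust-SE arm-by-time GEE gives 0.076, 0.078 and 0.073 for the three analyses. Anxiety has the same visits as burden, so the same figures apply.

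**Step 4: depression (two follow-ups).**

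| Tests that count | r = 0.3 | r = 0.5 | r = 0.7 |
|---|---|---|---|
| Adjusted, T1 and T2 only | 0.096 | 0.094 | 0.093 |
| Change and adjusted at T1 and T2, plus change-type or baseline-adjusted GEE | 0.15 | 0.14 | 0.13 |
| Same, with GEE averaging in baseline | 0.172 | 0.167 | 0.161 |

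The full-data simulation of the middle row gives 0.154, 0.141 and 0.139. For reference, five independent tests would give 1 − 0.95⁵ = 0.226, so the correlation between the tests removes a good part of the excess.

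**The case against.** **Ranking belongs in an analysis plan.** Designating analyses and listing covariates is often left to a SAP, and this is one paragraph of a journal article. That would answer a complaint about missing detail. Here, however, the article itself sets out overlapping tests and presents them unranked. A later document would be choosing among analyses already published on an equal footing, in a trial that is already enrolling.

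**The steps have different roles.** The t tests come first, the regression handles confounding, and the GEE addresses whether the effect lasts. One could even read the last GEE sentence as making it the main model. This stands in part, and the GEE's stated purpose should be acknowledged. It sets no precedence, though. The GEE is extended to every outcome with the arm indicator as main term, and burden and anxiety have a single follow-up, so for them it cannot assess persistence between follow-ups.

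**The size can be overstated.** A reader might infer that the error rate is 0.114/0.05 = 2.3 times alpha for burden and 0.168/0.05 = 3.4 times for depression (0.168 from a 400,000-draw run at r = 0.5; 0.167 in the table). Those figures arise only if the GEE counts the pre-randomisation baseline as outcome. The section's wording permits that form but does not specify it, so they are upper values. No section says that any single p<0.05 would be claimed, so even the lower figures describe what the plan allows, not what it declares.

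**The visit gap is narrow.** This is correct: it concerns depression alone.

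**Conclusion.** The point holds. The plan puts each primary outcome through several unranked analyses, and for depression it also leaves the deciding visit open. The false-positive rate for one outcome is about 0.07–0.08 for burden (up to 0.11) and about 0.13–0.15 for depression (up to 0.17), against 0.05. The upper values apply if the GEE averages baseline into the arm effect. All of these figures rest on assumed correlations of 0.3 to 0.7, on a between-arm change test in place of the paired t test, and on any significant result being claimable. Freedom in choosing confounders beyond the fixed models simulated is not counted and could only add to them. The document does not support reading this as evidence that the sponsor intends to select results, nor as an open visit for burden or anxiety. Multiplicity across the three primary outcomes is a separate matter.

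**What to change.** State in the Statistical analyses section that the deciding contrast for each primary outcome is the iSupport-minus-control difference at T2 (6 months, the visit already used for the sample size). Estimate it from one prespecified model adjusted for that outcome's T0 value and the two stratification factors, sex and relationship (spouse/other), and test it at two-sided 0.05. A GEE with a T2 contrast and the same covariates would serve equally well; what matters is that one is named.

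State also that the t tests, models with further confounders, the other GEE contrasts (persistence of effect) and the T1 CES-D10 comparison are supportive and cannot by themselves carry a claim of effectiveness.

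The cost is a few sentences, with no new data or participants. The price is that an effect seen only at T1, or only in a supportive model, can no longer be claimed as a primary success. The change brings the error rate for one outcome back to 0.05; it does not settle multiplicity across the three primary outcomes.

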Behavioral Problems RMBPC (6, 0–4, 0–24)^g^	Revised Memory and Behavioral Problems Checklist	Rs = 0.29, .31, .26; ps < .01 correlations between subscales and caregiver depression (CES-D) and burden (Caregiver Stress Scale)	Cronbach’s α values are: .75 for frequency and .76 for reaction for memory problems .82 and .77 for depression and .62 and .70 for disruptive behavior	X		X
Functional status of person with dementia AD^h^	Informant Questionnaire on Cognitive Decline in older people (AD8)	*r* = 0.75	Cronbach’s α = 0.84	X		X
Demographic variables caregiver’s age, caregiver sex, relationship to the person with dementia (spouse, adult child, or other family member), level of education, living arrangement (living together or apart from the person with dementia)				X		

^a^Zarit S, Reever KE, Back Peterson. Relatives of the impaired elderly: correlates of feelings of burden. The Gerontologist. 1980;20:649–655

^b^Björgvinsson T, Kertz SJ, Bigda-Peyton JS, McCoy KL, Aderka IM. Psychometric properties of the CES-D 10 in a psychiatric sample. Assessment*.* 2013;20: 429–436

Radloff LS. CES-D scale: a self report depression scale for research in the general populations. Applied Psychological Measurement*.* 1977;1:385–401

^c^Spitzer R, Kroenke K, Williams JBW, Lowe B. A brief measure for assessing generalized anxiety disorder. Arch Inern Med*.* 2006;166:1092–1097

^d^Brooks R, Rabin R, de Charro F (Ed.). The measurement and valuation of health status using EQ-5D: a European perspective: evidence from the EuroQol BIO MED Research Programme. Rotterdam: Kluwer Academic Publishers; 2003

^e^Pearlin LI, Schooler C. The structure of coping. Journal of Health and Social Behavior*.* 1978;19:2–21

^f^Steffen A, McKibbin C, Zeiss A, Gallagher-Thompson D, Bandura A. Revised Scale for Caregiving Self-Efficacy: reliability and validity studies. J Gerontol B Psychol Sci Soc Sci*.* 2002;57: P74–P86

^g^Teri L, Truax P, Logsdon R, Uomoto J, Zarit S, Vitaliano PP. (1992). Assessment of behavioral problems in dementia: The Revised Memory and Behavior Problems Checklist (RMBPC*).* Psychology and Aging*.* 7(4):622–31.

^h^Galvin JE, Roe CM, Powlishta KK, Coats MA, Muich SJ, Grant E, Miller JP, Storandt M, Morris JC. The AD8: a brief informant interview to detect dementia. Neurology. 2005; 65:559–564

^h^Galvian JE, Roe CM, Xiong C, Morris JC. Validity and reliability of the AD8 informant interview in dementia. Neurology. 2006;67:1942–1948

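### Covariate adjustment is framed as open-ended confounder control and commits neither the baseline outcome nor the stratification factors to the models

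*Protocol article*

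**What the plan says.** - **Purpose of adjustment.** Statistical analyses says of the regressions: "By using multiple regression analyses, we can correct for possible confounders". Of the GEE models, one per outcome with an arm indicator as the main predictor, it says: "Potential confounders will be added to these models". It gives no list.
- **Randomization.** Allocation is "stratified by sex and relationship to the care recipient (spouse/other) with a block size of 2".
- **Candidate covariates.** The Covariates section names, among others, "their sex, their relationship to the person with dementia (spouse, adult child, or other family member", so relationship has three categories there and two in the stratification. Table 1 repeats these demographics under the heading "Confounders/modifying Variables".
- **Repeated candidates.** The same part of Table 1 holds the "Revised Memory and Behavioral Problems Checklist" (RMBPC) and the AD8. Each is marked twice, which reads as T0 and T2.
- **Baseline comparison.** The Randomization section says: "Baseline characteristics of individuals randomized to either of the two conditions will be compared to ensure that randomization was successful". Statistical analyses adds that "missing data and unbalance will be evaluated".
- **Baseline outcome.** None of these places names the T0 value of an outcome as a covariate. The Sample size calculation section does size the trial on change in Zarit burden at 6 months.

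**The concern.** In a randomized trial, baseline variables differ between arms only by chance, so confounding control is the wrong reason to adjust. The sound reasons are prognostic strength and respect for the stratified design. On those grounds the first covariates to fix are the T0 outcome, usually the strongest predictor of its own follow-up value, and the stratification factors. The article describes candidate covariates but omits the first and leaves the second optional.

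Three things are at stake:

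- **Precision.** An analysis that uses T0 inefficiently, or not at all, gives wider intervals than the data allow.
- **Analyst discretion.** An open set of possible confounders lets the estimate depend on choices made after the data are seen.
- **Bias.** Ten of the 23 iSupport lessons deal with challenging behavior, so the program can change behavior ratings at T2. A T2 rating is then partly a consequence of treatment, and adjusting for it would remove part of the effect.

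**Working it through.** **Inputs from the document.** Two-sided alpha 0.05, power 80%, standardized effect 0.33, and 80 per group before the 30% increase (Sample size calculation). Lessons per theme are 1 + 4 + 3 + 5 + 10 = 23, ten of them on challenging behavior (description of iSupport).

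**Assumed.** The T0–T2 correlation r of the outcome is not given; 0.5, 0.6 and 0.7 are used. The effect of 0.33 is taken in SDs of the raw score.

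**1. The plan's own figure.** For two independent means, n per group = 2 × ((1.960 + 0.842)/0.33)² = 144.1, so 145, not 80. Baseline information would bring this down to 80 only if
- 144.1 × (1 − r²) = 80, that is r = 0.67 (ANCOVA), or
- 144.1 × 2(1 − r) = 80, that is r = 0.72 (change score).

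No such r is stated. The failure to reproduce 80 is a separate sample-size matter. It matters here only because it shows how much depends on the way T0 is used.

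**2. Power at 80 analysed per arm.** The noncentrality is 0.33/√(2V/80), where V is the outcome variance relative to the raw score: 1 for the follow-up score alone, 2(1 − r) for change, and 1 − r² for ANCOVA. Power is from the noncentral t; the normal approximation is about half a point higher.

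| r | Follow-up only | Change score | ANCOVA on T0 |
|---|---|---|---|
| 0.5 | 2.09 → 55% | 2.09 → 55% | 2.41 → 67% |
| 0.6 | 2.09 → 55% | 2.33 → 64% | 2.61 → 74% |
| 0.7 | 2.09 → 55% | 2.69 → 76% | 2.92 → 83% |

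The standard error of ANCOVA relative to change is √((1 + r)/2): 0.87, 0.89 and 0.92. This ratio does not depend on the scale in which 0.33 is expressed.

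**3. Ignoring the strata.** If the strata explain a share R² of outcome variance (assumed), a test that ignores them has actual size 2 × (1 − Φ(1.96/√(1 − R²))). That is 0.044 at R² = 5% and 0.039 at 10%. The test is mildly conservative.

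**4. Entering T2 RMBPC.** Suppose iSupport lowers T2 RMBPC by 0.2 SD and burden rises by 0.3 to 0.5 SD per SD of RMBPC, with no other common cause (all assumed). A total effect of −0.33 would then be estimated as −0.33 + 0.2 × 0.3 = −0.27, down to −0.33 + 0.2 × 0.5 = −0.23. With T0 values this bias does not arise.

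**The case against.** Three stronger readings are tempting, and the document supports none of them.

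- **That the stratification factors are left out.** Both are named in the Covariates section and again in Table 1. What is missing is a commitment to put them in the models, and in the two-category form used for stratification.
- **That covariates will be chosen by observed imbalance.** The baseline comparison is given another purpose, checking the randomization, and no sentence makes it a selection rule. The link is an inference from neighboring sentences.
- **That T2 RMBPC or AD8 will be adjusted for.** The marks in Table 1 show when an instrument is collected, not which value enters a model, and the heading covers modifiers as well as confounders.

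It is also fair to object that 55% for an unadjusted follow-up score is a convenient comparator. The trial is sized on change, and a GEE model may carry T0 as one of the repeated measures. Against a change score, the gain at r = 0.7 is 83 − 76 = 7 points, not 28. This stands, so the change score is the main comparator here. How T0 would enter the GEE is not described, so no firm loss can be attributed to that model.

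Finally, this is a condensed article, and an exact covariate list may properly sit in an analysis plan. That excuses the missing detail. It does not repair the stated reason for adjustment, which would steer such a list the wrong way.

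**Conclusion.** The point holds as an improvement available at no cost, not as an error that invalidates the analysis. The confounder rationale is poorly suited to a randomized trial, the T0 outcome is not named as a covariate, the stratification factors are not committed, and the timing of RMBPC and AD8 is open.

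Relative to a change score, adjusting for T0 adds about 12, 10 and 7 percentage points of power at r = 0.5, 0.6 and 0.7. This assumes 80 analysed per arm and a raw-score effect of 0.33 SD. All three correlations are assumptions, and the realized gain depends on how T0 would otherwise have been used. Ignoring the strata costs little. The bias from T2 behavior scores is a risk to close off, not a planned step, and its size above rests wholly on assumed values.

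**What to change.** Replace the confounder wording in Statistical analyses with a prespecified rule:

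- Every effect model includes arm, the T0 value of that outcome where collected, sex, and relationship coded spouse/other as in the randomization.
- Any further covariates are named in advance for their prognostic value. Baseline comparisons are reported descriptively and are not used to choose covariates.
- If RMBPC or AD8 enters an effect model, only its T0 value is used.

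The words where collected matter. As far as its layout can be relied on, Table 1 shows no T0 mark for EQ-5D, mastery or self-efficacy, so the authors should confirm which secondary outcomes have a baseline value.

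The cost is a change of wording. Sex, relationship, and the T0 values of the three primary outcomes, RMBPC and AD8 are already scheduled for collection.
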